
### Study Duration

The study duration for each patient will be 12 months, starting with the first dose of depot buprenorphine and ending with the last follow-up assessment at month 12 (t_4_). For matched control patients, the study starts with their baseline examination (after informed consent) and finishes with their participation at the 12-months-assement (t_4_).

Patient recruitment started in April 2020 with first-patient-first-visit. Patients will be recruited over a period of 18 months ending with last-patient-first-visit in September 2021. The individual patient data collection will take further 12 months (last-patient-last-visit in September/October 2022). The data collection, entry and processing of the last incoming CRFs and patient information, the scientific evaluations as well as the production of the final study report will require further six months. Thus, the study will be completed in March 2023 with a total study duration of 39 months.

### Selection and Treatment of Participants

Inclusion and exclusion criteria are listed below. Patients who are not eligible for the treatment with injectable subcutaneous depot buprenorphine according to Summary of Product Characteristics (SmPC) will be excluded from the depot buprenorphine arm, but can be part of the control group, if pairwise matching criteria apply. If a patient drops out from treatment with injectable depot buprenorphine (and returns to previous medication or give up OST at all) he or she should be followed up for the whole study period (unless he/she withdraw the study consent).

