### Study Design

The study objectives will be evaluated in a non-randomized prospective non-interventional observational study with control group design (treatment-as-usual, TAU). All OST patients with TAU (i.e., treated with any registered OST medication, but not with injectable depot buprenorphine (e.g., racemic methadone, levomethadone, sublingual buprenorphine or slow release oral morphine) can take part in the control group. In order to avoid a selection bias and to ensure an overall comparability of the patient groups (injectable depot buprenorphine vs. TAU), one suitable patient from the OST unit will be pairwise matched to each recruited depot buprenorphine patient. Matching variables are gender (male /female), duration of OST (years), take-home prescription (yes /no) and patients' functioning measured by the global assessment of functioning scale (according to percentiles measured by the Global Assessment of Functioning Scale, GAF). Prior to matching, all patients from each participating OST unit will be screened for these four criteria based on an anonymized list of patients. After inclusion of a depot buprenorphine patient, a respective OST patient who is not willing to switch to depot treatment will be asked to participate as control group patient. An overview of the study design is provided in Figure 1.

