#### Exclusion Criteria

##### For both arms

- Inability of the patient to participate in the study (e.g., due to severe mental impairment)- Missing patient-signed written informed consent (this means that patients who cannot give their consent will be excluded, even if their legally acceptable representatives provide the willingness of the patient to participate).

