##### For the depot buprenorphine arm

- Missing eligibility for OST with injectable subcutaneous depot buprenorphine according to (SmPC)- OST with injectable subcutaneous depot buprenorphine within the last 3 months.

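### Matching does not ensure a comparable control group: patients who could not receive depot buprenorphine, or who recently stopped it, may serve as controls

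*Protocol article*

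**What the plan says.** All places are in the protocol article.

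- *Selection and Treatment of Participants*: patients not eligible for depot under the SmPC "will be excluded from the depot buprenorphine arm, but can be part of the control group, if pairwise matching criteria apply".
- *Exclusion Criteria, For the depot buprenorphine arm*: two items stand here and nowhere else, namely "Missing eligibility for OST with injectable subcutaneous depot buprenorphine according to (SmPC") and "OST with injectable subcutaneous depot buprenorphine within the last 3 months".
- *Exclusion Criteria, For both arms*: only "Inability of the patient to participate in the study (e.g., due to severe mental impairment") and missing consent.
- *Study Design*: the control group is open to patients "treated with any registered OST medication, but not with injectable depot buprenorphine". In practice, "a respective OST patient who is not willing to switch to depot treatment will be asked to participate as control group patient".
- *Study Design*, purpose of the pairing: "In order to avoid a selection bias and to ensure an overall comparability of the patient groups". "Matching variables are gender (male /female), duration of OST (years), take-home prescription (yes /no"), and functioning by GAF percentile.
- *Secondary Outcome Analyses*: depot and control are compared in a mixed model with baseline OSTQOL and the pair term as covariates.
- *Abstract*, Discussion paragraph: the matching is said to permit conclusions about the effects of different OST medications.

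**The concern.** A matched comparison can speak to the effect of a treatment only where both members of a pair could have received it. A control who was ineligible for depot has no possible counterpart in the depot arm, because every depot patient had to be eligible. This gap in overlap is written into the entry rules, and matching on other variables cannot close it.

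The recent stopper is a different case. That patient has tried the medication under study and left it, yet counts as treatment as usual. The control definition refers to current medication, so nothing in the article keeps such a patient out.

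At stake is how the depot-versus-control results may be read. The article presents the pairing as the safeguard for those comparisons and does not mention either asymmetry among its limitations.

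**Working it through.** **1. The two criteria, arm by arm**

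| Criterion | Depot arm | Control arm | Matching variable? | In the planned model? |
|---|---|---|---|---|
| Not eligible for depot under the SmPC | excluded | expressly allowed | no | no |
| Depot use in the last 3 months | excluded | no exclusion listed | no | no |

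The first row rests on an explicit sentence. The second rests on where the criterion is listed: under the depot arm, and absent from the both-arm list. Baseline OSTQOL, the pair term and GAF can absorb some difference in prognosis that is visible at baseline. None of them records eligibility or earlier depot use.

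**2. Which endpoints use control data**

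The primary endpoint is the change in OSTQOL total score within the depot group, so no control data enter it. Of the ten secondary outcomes in Table 1, six compare depot with control: OSTQOL, CSQ-8, substance use, BSI-18, social participation and cost-effectiveness. *Secondary Outcome Analyses* also provides group tests in connection with retention.

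**3. The plan's own figures** (*Sample Size Calculation*)

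- Within-group test, d = 0.25, two-sided 5%, power 80%. The normal approximation is (1.960 + 0.842)² / 0.25² = 125.6. The exact paired t-test gives n = 128 (power 0.8015), as stated.
- Drop-out of 40%: 128 / 0.6 = 213.3, stated as 213.
- Between groups, with 128 completers per arm: (1.960 + 0.842) × √(2/128) = 0.350, as stated.

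The first two figures do not involve the make-up of the control group. The third describes power, not bias.

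**4. What would be needed to size the bias**

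Let s be the share of such controls, and b the difference in their month-12 OSTQOL, in SD, that remains after matching and adjustment. The spurious between-group difference is then s × b in size, with a sign opposite to the shift in the controls. The document gives neither s nor b. Purely as assumptions:

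| s | b = 0.25 | b = 0.5 | b = 0.8 |
|---|---|---|---|
| 10% | 0.025 | 0.05 | 0.08 |
| 20% | 0.05 | 0.10 | 0.16 |
| 30% | 0.075 | 0.15 | 0.24 |
| 50% | 0.125 | 0.25 | 0.40 |

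The range runs from negligible to above the detectable 0.35, and that value is exceeded only in the most extreme cell. The table shows how the bias would scale. It is not an estimate for this study.

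**The case against.** The rule on ineligible patients is stated openly and looks deliberate. The comparator is routine OST care, and the Discussion defends a mixed control group as part of a naturalistic approach. It also names the absence of randomization as the main limitation, concedes that switchers may differ from other patients, and there claims only to minimize selection bias. The 3-month exclusion has a special purpose in the depot arm: the baseline should precede depot exposure for the primary endpoint. Depot was new on the market, so recent stoppers may be few.

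Much of this stands, and it limits the point to the secondary comparisons. It does not remove the point. A naturalistic aim justifies controls on many different OST medications. It does not explain why controls should lie outside the population that could be treated. The general disclosure does not name either asymmetry, and *Study Design* still claims more for the matching than the Discussion does.

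A reader might infer more than the document supports:

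- *That the bias favours depot.* Nothing in the article shows that ineligible patients or recent stoppers do worse. A stopper could enter at a low point and improve, which would work against depot.
- *That Study Design and Selection and Treatment of Participants contradict each other*, one describing controls as unwilling and the other admitting the ineligible. A patient can be both. One section says whom staff approach, the other who is admissible. Unwillingness simply does not screen out either kind of patient.

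**Conclusion.** The point holds in a limited form. The entry rules admit two kinds of control that the depot arm excludes, and neither the matching nor the planned model accounts for them. The pairing therefore does not ensure comparability. It would go too far to say that the control group is not comparable, because the document does not show how many such controls there would be.

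Size and direction cannot be derived. The conclusion rests on the text of the criteria and not on any assumed share or outcome shift. It also assumes that the full protocol adds no prior-depot exclusion for controls. The rule on ineligible patients needs no such assumption.

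The within-depot primary endpoint and the sample size are untouched. This is a cheap improvement to the secondary comparisons and to the wording of the conclusions, not a threat to the main result.

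**What to change.** 1. Record two items from the chart for every control: eligibility for depot under the SmPC at baseline, and depot use in the 3 months before baseline. *Variables* names neither.
2. Apply both existing depot-arm exclusions to controls still to be enrolled. By *Study Duration*, recruitment ran from April 2020 to September 2021, so steps 1 and 3 may carry most of the weight.
3. For the depot-versus-control endpoints, prespecify an analysis restricted to pairs whose control was eligible and had no depot use in the last 3 months, reported alongside the full-set analysis. State what happens to a depot patient whose control is removed: drop the pair, or keep the patient unpaired in the mixed model.
4. Soften the statement that matching avoids selection bias. Willingness to switch still differs between the groups by design, and this fix does not change that.

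**Cost.** Two chart items, a smaller control pool in small units, and some precision. If a share s of controls is removed from 128 completers per arm, the detectable effect (ignoring within-pair correlation, in line with the reproduction of the plan's 0.35) becomes:

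- pairs dropped: 0.350 / √(1 − s)
- depot patients kept unpaired: 2.80 × √(1/128 + 1/(128(1 − s)))

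For an assumed s of 10%, 20% or 30% this gives 0.37, 0.39 or 0.42 with pairs dropped, and 0.36, 0.37 or 0.39 with depot patients kept. Because the full-set analysis is reported as well, that loss applies to the restricted analysis only.

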#### Inclusion Criteria

##### For both arms

- Opioid dependence (F11.2) according to ICD-10- Minimum age of 18 years- Ability to follow the study procedures- Signed written informed consent. The approved informed consent form will adhere to the ethical principles that have their origin in the Declaration of Helsinki.

##### For the depot buprenorphine arm

- Willingness to be treated with injectable subcutaneous depot buprenorphine.

#### Exclusion Criteria

##### For both arms

- Inability of the patient to participate in the study (e.g., due to severe mental impairment)- Missing patient-signed written informed consent (this means that patients who cannot give their consent will be excluded, even if their legally acceptable representatives provide the willingness of the patient to participate).

##### For the depot buprenorphine arm

- Missing eligibility for OST with injectable subcutaneous depot buprenorphine according to (SmPC)- OST with injectable subcutaneous depot buprenorphine within the last 3 months.

### Patient Recruitment

The study will be carried out in OST units (specialized primary care practices or addiction outpatient clinics) with OST physicians experienced in the substitution treatment of opioid-dependent patients. All patients who start OST with injectable depot buprenorphine or who have the intention to switch from a previous OST medication to injectable depot buprenorphine will be informed by the OST physician about the possibility to participate in the study. The decision to be treated with injectable depot buprenorphine has to be made in advance and independently of study participation. All patients who fulfill the inclusion criteria will receive the detailed study information. The matching and recruiting process will be documented by lists, including the assignment of the patient and the code number. The recruitment lists will be kept in the OST unit and will be treated confidential. Only staff from the OST unit will have access to the recruitment lists. The inclusion of a patient will be documented on a specific form and will be faxed or sent as a scan to the study center (ZIS).

### Treatment

The depot arm of the study will include opioid-dependent patients who are willing to switch or to initiate OST with one of two injectable depot buprenorphine formulations (once weekly or once monthly). Thus, this includes newly admitted patients who are starting with OST, as well as patients who are already in treatment (e.g., with racemic methadone, levomethadone, sublingual buprenorphine, slow release oral morphine). The participation in the study is voluntary and non-participation will not incur disadvantages neither for the physician (or the OST unit) nor for the patient. In this respect, there will be no increased risk resulting from study participation. Patients who were facing problems with their previous OST medication might benefit from study participation, and probably show an increased acceptance and willingness to use subcutaneous, injectable depot buprenorphine. Further, OST providers might benefit from expanded, more individualized therapeutic options for OST patients. Based on the clinical experiences gained so far, injectable depot buprenorphine is highly accepted by patients, and its side effect profile is comparable to sublingual buprenorphine with few, mild and reversible injection site reactions (17).

### Assessment and Timelines

All data will be collected in case-report-forms (CRFs) including documentation sheets for clinical routine data and questionnaires for OST providers and patients. After baseline (t_0_), follow-up assessments will be made on month 1 (t_1_), month 3 (t_2_), month 6 (t_3_), and month 12 (t_4_). For the case that OST ends prematurely (before the end of the 12-month study period), study participation continues, and the patient will be asked to take part in the remaining follow-up assessments. All patients will receive reimbursements of € 10,-for each assessment.

### End of Study

After 12 months, with the date of the corresponding documentation and patient survey, the study will end for each patient. As the study participation is voluntary, the patient can prematurely terminate the study at any time. After the study, OST will be continued as needed. Neither study participation nor study termination will have implications on any treatment condition or on the future course of OST.

### Data Analysis

#### Study Sample

Patients will be described (if necessary separated by gender) according to their baseline characteristics and OST data. For categorical data relative frequencies, for continuous data means and standard deviations will be applied.

#### Primary Outcome Analysis

The main analysis will be carried out according to the intention-to-treat principle (ITT), considering all patients who have started the substitution treatment with injectable depot buprenorphine. The primary outcome measure is the difference of OSTQOL (20) scores between baseline (t_0_) and month 12 (t_4_) in the depot group. The average OSTQOL mean score will be compared between these time points and analyzed for statistical significance using dependent *t*-tests. It is tested against the statistical null hypothesis (H0) of a decrease or no change in the OSTQOL mean score. The alternative hypothesis (H1) consists in a significant improvement of the OSTQOL mean score, which corresponds to an improvement in quality of life of the patients.

H0: M (Month 12) ≤ M (baseline) (OSTQOL mean score at 12 months ≤ baseline OSTQOL mean score)H1: M (Month 12) > M (baseline) (OSTQOL mean score at 12 months > baseline OSTQOL mean score).

The hypothesis will be tested two-sided at a significance level of *p* < 5%. The statistical analyses will be made according to the intention-to-treat (ITT) as well as to the per-protocol (PP) principle. The PP sample is defined by all patients who have undergone OST with injectable subcutaneous depot buprenorphine for at least 12 months and for whom sufficient baseline and 12-month data are available. The ITT sample comprises all patients who provided a written consent, who have undergone the baseline assessment, and–for patients in the depot study arm–who have received the first dose of injectable depot buprenorphine. For the ITT analysis, data from all study patients will be used independently of their status in or out of treatment with injectable depot buprenorphine. Missing values at the 12-month time point will be replaced by missing imputation procedures. These may either include last observation carried forward (LOCF) approaches or longitudinal mixed model analyses using all available follow-up assessments. The choice of imputation procedures for the ITT analysis will depend on the proportion of missing values at the 12-month time point as well as the quantity of available data at 3-month and 6-month follow-up, and will be determined by sensitivity analyses.

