### Variables

The following variables will be collected at baseline (t_0_) and follow-ups [month 1 (t_1_), 3 (t_2_), 6 (t_3_), 12 (t_4_)]:

- **Sociodemographic data** including gender, age, current housing, work, family status/partnership.- **Health data** will be collected using the Opiate Treatment Index-Health Symptom Scale (OTI-HSS), a symptom checklist to assess the patient's current health status with regard to medical problems that opioid users often develop (e.g., injection-related problems, cardio/respiratory problems, musculoskeletal problems, neurological problems, gastro-intestinal problems (21, 22).- **OST data** (medication, doses) routinely collected by the OST practice/clinic.- **Quality of life** will be measured by the OSTQOL, a disease-specific instrument for measuring quality of life among patients in OST (20). First analyses in developmental processes of the OSTQOL showed acceptable internal consistencies of all subscales (personal development, psychological stress, social contacts, material well-being, OST and discrimination), with Cronbach's alpha between 0.75 and 0.88, as well as a good convergent and discriminant validity of the instrument (20).- The **patient acceptance** of injectable depot buprenorphine will be measured along the four key dimensions of the Treatment Satisfaction Questionnaire for Medication (TSQM-14) (effectiveness; side effects; convenience and global satisfaction).- The **Client Satisfaction Questionnaire (CSQ-8)** will be used to measure the patients' satisfaction with the overall OST care. The short 8-item instrument has been frequently used in substance use research including OST (23, 24) and has shown a high internal consistency and concurrent validity (25).- Parts (heroin craving, acceptance of the OST medication) of the **Opiate Dosage Adequacy Scale (ODAS)** will be used to measure the adequacy of opioid doses among the patients in the depot buprenorphine group. The ODAS consists of six domains (heroin consumption, narcotic blockade, mental and somatic opiate withdrawal syndrome, craving for heroin, and OST overdosing) including items which can be answered by the patient. Scores range between 1 (worst) and 5 (best). Cut-off scores of 3 or less in any ODAS domain will be regarded as not adequately dosed. The ODAS was found to have a good validity and reliability to measure and assess buprenorphine dose adequacy in the context of OST (26).- Data on **substance use** will be collected on the basis of patient self-report using the drug and alcohol use domain of the European Addiction Severity Index (EuropASI) (27). The data on substance use will be complemented by urine samples collected within routine OST care. The urine samples will be tested for heroin, non-prescribed substitutes, cocaine/crack, amphetamine, cannabis and benzodiazepine use.- **The psychological distress** among the patients will be measured by the Brief-Symptom-Inventory 18 (BSI-18), (28). The questionnaire comprises 18 items on physical and psychological symptoms, rated on a 5-point Likert scale (0 = not at all; 4 = very much) with regard to the last 7 days, and yields 3 sub-scores for depression, anxiety, and somatization, as well as an overall Global Severity Index (GSI).- **Social participation** will be measured by a self-developed short questionnaire including questions on the number and kind of social activities (e.g., recreational or physical activities, activities with friends, family) within the last week.- Data to calculate the **retention in treatment** will be collected by the date of ending OST or changing OST medication. The dates will be collected retrospectively by the treatment staff at any follow-up timepoint of the study. Retention in treatment will be calculated by dividing the number of patients in each study arm at each follow-up visit by the total number of patients in each study arm at baseline.- Quality-adjusted life years (QALYs) will be used for the **cost-effectiveness analysis**. Respective data will be collected with the EuroQOL five dimensions questionnaire (EQ-5D) (29).

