### Sample Size Calculation

A study by Apelt et al. (30) showed a significant improvement in health-related quality of life (measured by SF-36) with an average effect size of *d* = 0.40 after 12 months among patients who switched from (levo-) methadone or buprenorphine to buprenorphine/naloxone. A study by Karow et al. (31) found effect sizes in the improvement of quality of life measured by MSQOL in patients treated with diamorphine between *d* = 0.73 (after 6 months) and *d* = 0.80 (after 12 months).

An α-error of 5% and a statistical power of 80% (β-error = 20%) will be used. In our study we anticipate a smaller effect size of d = 0.25 which will result in a minimum number of *N* = 128 patients. Further we estimate a drop-out rate of 40% until month 12 (t_4_) resulting in a sample size of *N* = 213 patients treated with injectable depot buprenorphine. Considering the same number of patients in the matched control group, the total sample size is *N* = 426. Under the conditions of an α-error of 5% and a statistical power of 80% this sample size allows for detection of statistically significant differences in group comparisons with an effect size of *d* = 0.35 or higher.

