### Drop-Outs

Patients who cannot be analyzed (i.e., missing baseline and follow-up data, not starting treatment with injectable depot buprenorphine) will be excluded from the data analyses. If either the medication with injectable depot buprenorphine or OST treatment or study participation (or both) is discontinued, the reason for the termination or circumstance will be documented. Patients who change from the depot group to the control group or vice versa will be followed-up as long they withdraw their study participation or terminate OST (drop-out). In both cases the reasons will be documented. A drop-out analysis will be performed to determine potential drop-out criteria.

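### The missing-data methods named for the primary ITT analysis do not mention depot status, so the within-group change is overstated if patients who leave depot do worse and miss month 12 more often

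*Protocol article*

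**What the plan says.** The endpoint has no comparator. Under Primary Outcome Analysis, "The primary outcome measure is the difference of OSTQOL (20) scores between baseline (t_0_) and month 12 (t_4_) in the depot group", to be "analyzed for statistical significance using dependent *t*-tests". The ITT set is every depot patient with consent, a baseline assessment and a first dose, and "data from all study patients will be used independently of their status in or out of treatment with injectable depot buprenorphine". The question is therefore how all starters fare at month 12, including those who have left depot.

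The same section says that missing month-12 values will be replaced. It names LOCF and "longitudinal mixed model analyses using all available follow-up assessments" as possibilities. The choice is to depend on the proportion missing at month 12 and on how much month-3 and month-6 data exist, and is to be settled by sensitivity analyses. Depot status appears in none of this.

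Depot status is nevertheless planned data. Under Variables, the data for retention "will be collected by the date of ending OST or changing OST medication"; treatment staff collect these dates at the follow-up timepoints. The Drop-Outs section has reasons for stopping documented and adds: "A drop-out analysis will be performed to determine potential drop-out criteria". It links that analysis to no estimate.

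On follow-up, Selection and Treatment of Participants keeps leavers in the study for the whole period unless they withdraw consent. Assessment and Timelines continues assessments after OST ends. The Drop-Outs section can be read as ending follow-up, for patients who change group, once OST ends.

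**The concern.** Month-12 scores after leaving depot belong to the ITT question, but they may also be the scores most often missing. A mixed model that knows only earlier OSTQOL scores treats a lost leaver like any other patient with the same history. Most patients measured at month 12 may be stayers, so the filled-in value leans towards the stayers' course. LOCF goes wrong by another route: it holds the leaver at his or her own last score, which was often taken while on depot.

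The primary result is a single-arm change, so no control group can absorb such a bias. It passes directly into the estimate and the test, and moves the ITT answer towards the stayed-on-depot answer that the per-protocol analysis already covers. Settling the choice between LOCF and the mixed model does not remove the problem.

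**Working it through.** **The plan's own figures.** For a paired t-test with d = 0.25, two-sided 5% and 80% power, the noncentral t gives N = 128, as stated. Dividing by (1 − 0.40) gives 213.3, against 213 stated. The sample size is not in question. It supplies two inputs: 40% lost by month 12 and a planned effect of 0.25 SD.

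**Assumed inputs.** The article says nothing about how leavers fare or how often they are measured. I assume that 40% leave depot, 40% of month-12 scores are missing, stayers gain 0.25 and the within-patient correlation is 0.6. Units are SDs of the change.

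**Hand check.** Let p be the share leaving, g_S and g_L the changes of stayers and leavers, and r_S and r_L the shares measured.

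- True ITT change = (1 − p)·g_S + p·g_L
- Mean of those measured = [(1 − p)·r_S·g_S + p·r_L·g_L] / [(1 − p)·r_S + p·r_L]

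Case (a): g_L = 0, r_L = 0.25, r_S = 0.833. Missing = 0.4 × 0.75 + 0.6 × 0.167 = 0.40. True change = 0.6 × 0.25 = 0.15. Measured mean = (0.50 × 0.25) / (0.50 + 0.10) = 0.21.

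Case (b): as (a), with g_L = −0.375. True change = 0.15 − 0.15 = 0.00. Measured mean = (0.125 − 0.0375) / 0.60 = 0.15.

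Case (c): g_L = 0, r_L = 0.50, r_S = 0.667. True change = 0.15. Measured mean = (0.40 × 0.25) / 0.60 = 0.17.

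Case (d): g_L = 0, no leaver measured, all stayers measured. True change = 0.15. Measured mean = 0.25.

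**Simulation** (213 patients, OSTQOL at baseline and months 3, 6 and 12, 1,500 runs per case):

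| Case | True | Mixed model, no status | LOCF | Mixed model with on/off-depot term |
|---|---|---|---|---|
| (a) | 0.15 | 0.21 | 0.18 | 0.15 |
| (b) | 0.00 | 0.15 | 0.14 | 0.00 |
| (c) | 0.15 | 0.17 | 0.15 | 0.15 |
| (d) | 0.15 | 0.25 | 0.21 | 0.25 (term not estimable) |

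The mixed model lands on the hand-calculated mean of those measured. Where some leavers are measured it overstates by 0.02 to 0.15 SD, and LOCF by 0.00 to 0.14 SD. Adding status removes the mixed-model bias in (a) to (c), but not in (d).

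**A second simulation with different inputs** (stayers +0.40, leavers 0, visit correlations 0.5 to 0.6) has a true change of 0.6 × 0.40 = 0.24. The mixed model without status gives 0.28, 0.31 and 0.34 when 50%, 60% and 75% of leavers are missing, a bias of 0.04, 0.07 and 0.10. If leavers and stayers are missing equally often, the bias is about 0.01 to 0.02.

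**Effect on the test.** With stayers +0.20 and leavers −0.30, the true change is 0.6 × 0.20 − 0.4 × 0.30 = 0. For the same three missingness rates, the mixed model gives 0.05, 0.08 and 0.12. With a standard error of about 0.08, the chance of a significant result in favour is P(Z > 1.96 − bias/0.08): about 9%, 17% and 32%. The simulated rates are about 9%, 16% and 30%, instead of 2.5%.

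**The case against.** The strongest reply is that the point rests on silence. The article lists no model terms, its wording on the methods is open rather than a closed list, it plans sensitivity analyses, and Table 2 includes retention at every follow-up. Covariates of an imputation model are commonly left to a fuller document. This stands to the extent that one can say only that status is not mentioned, not that it is excluded. It does not dispose of the point: the article itself sets out candidate methods and a selection rule, and that rule looks at quantities of data and not at the variable that separates the ITT question from the on-treatment one.

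Second, nothing in the article shows that leavers do worse or are missing more often. They may return to their previous medication, and the Introduction counts preparation for regular OST termination among the uses of depot. That stands; the size of the bias is conditional.

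A reader might also infer more than the documents support:

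- That both methods credit leavers with the stayers' gain. LOCF borrows from nobody; a patient with only a baseline score gets zero change.
- That the mixed model credits that gain in full. Leavers who are followed also inform the model, so the borrowing is partial unless none of them is measured.
- That status is known for everyone. It is planned for all, but consent can be withdrawn, and the Drop-Outs wording may end follow-up when OST ends.
- That adding status always cures the bias. Case (d) shows that it cannot when no leaver is measured.

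**Conclusion.** The point holds in conditional form. The plan asks an on-or-off-depot question, names filling-in methods that do not mention depot status, and plans to collect that status. If leavers do worse and miss month 12 more often, the primary change is overstated by about 0.02 to 0.15 SD with the mixed model and about 0.00 to 0.14 SD with LOCF, under 40% leaving, 40% missing and at least some leavers measured. Against a planned 0.25 SD the upper end is material, and a true change of zero can be declared an improvement well above the nominal rate. If missingness does not depend on leaving, the mixed-model bias is negligible, about 0.01 to 0.02 SD. The leavers' courses and the missingness split are assumptions, not trial figures. The change should be made because the data are already planned and the cost is small; the documents do not show that the result will be biased.

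**What to change.** Under Primary Outcome Analysis, make the primary ITT method multiple imputation of month-12 OSTQOL from baseline, month-3 and month-6 OSTQOL plus on-/off-depot status at each visit. Lost leavers are then imputed from followed leavers. Combine the paired comparison over the imputations. Separate off-depot from out-of-OST, or add further predictors suggested by the drop-out analysis, only if enough leavers are measured: with 40% of 213 leaving and 75% of those missing, about 0.40 × 213 × 0.25 = 21 leavers would have a month-12 score.

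Keep the mixed model without status as a sensitivity analysis. Add a delta-adjusted or reference-based sensitivity analysis in case few leavers have month-12 scores.

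Reconcile the Drop-Outs wording on follow-up after OST ends with Selection and Treatment of Participants and Assessment and Timelines, because the method depends on leavers' scores.

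Cost: wording and some programming, with no new data. The standard error rises somewhat, to about 0.08 to 0.10 SD from about 0.08 SD. That range was simulated by conditioning on baseline and depot status, not with the full imputation model.
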